### Analysis of the material

All anonymized information gathered in the study will be stored in a Castor database at Radboud University Medical Center. The database is protected with passwords, and the data will be deleted 15 years after the study is officially closed. Only the research group will get full access to the database. Participating hospitals will get access to add data from their own participating patients. More information about the data management for the Cast OFF-2 study can be requested from the corresponding author on reasonable request.

### Statistical analysis

Descriptive analyses with median, range, and percentage will be used to describe demographic variables and outcomes such as age and gender. We will analyze the percentage of protocol violations and the willingness to participate from participating patients, hospitals, and physicians using a feedback evaluation. Patients will be asked to give feedback at the end of their follow-up period and physicians will be asked feedback after 6 months and 12 months.

A multivariate linear regression mixed model will be used to analyze the data from the different randomization groups and to account for clustering of repeated measurements within patients and within hospitals and time. We will analyze the effect of the intervention, in comparison with the usual care, on the PROs, return to activity, pain scores, and complication rate. We will adjust for confounding factors such as age, gender, and clinical parameters. The difference in complication rate will be determined using either a Fisher exact or a chi-square test, depending on the order of magnitude of the results. The difference in PCS-4 score, VAS score, and patient satisfaction will be determined using a *t*-test. The analysis will be performed by using the intention-to-treat model (according to the groups to which they were originally designed).

A cost-effective analysis will be performed additionally to the above-mentioned analyses. A budget impact analysis will be performed from various perspectives with the budgetary framework for the care as the base case perspective.

For missing data from patients who fulfilled the study, the available data will be analyzed if possible, for any interesting findings, and otherwise, the missing data will be imputed with replacement values using multiple imputation analysis.

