**Methods:**

This study will be performed using a multicenter randomized stepped wedge design in 12 centers. We aim to include in the study 440 patients with an isolated non-reduced DRF between the age of 18 and 85 years old. The patients in the intervention group will be treated with plaster cast immobilization for 1 week. Acceptability of the study protocol, patient-reported outcomes, quality of life, complications, pain catastrophizing score, pain and patient satisfaction, and cost-effectiveness will be measured. The total follow-up will be 12 months.

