### Measurements

For this study, the following main study parameters are gathered: functional outcome, return to activity, cost-effectiveness, and acceptability of the study protocol.
Patient-reported outcome (functioning and patient satisfaction): It is known that 1 week of plaster cast for a non-reduced DRF is safe. Secondary displacement of the fracture is not significantly different with longer plaster cast treatment [8, 9]. So, the most important question is whether 1-week treatment gives better functional results and higher patient satisfaction. The best measurement method to measure patient satisfaction and functional result is using a patient-reported outcome (PRO) [14]. In addition, PROs are better predictors of participation, such as the ability to return to work or perform daily activities, than more objective clinical measures.The Patient-Reported Wrist Evaluation (PRWE) is specifically designed for wrist and hand functioning. The PRWE is a reliable and valid measure of patient-rated pain and disability for wrist conditions [15, 16]. Furthermore, a validated Dutch version of the questionnaire is available [17]. The PRWE is a measurement with a score from 0 to 100, where 0 is no wrist function problems or pain. The minimal clinical important difference for PRWE is a difference of 11 points [18].The questionnaires will be sent to the patient after 6 weeks and 3, 6, and 12 months.Return to activity will be measured using the productivity costs questionnaire (iCPQ). Questions about return to work, leisure activities, household activities, and pain will be asked. These questions will be asked after 1 and 6 weeks, 6 months, and 1 year.A cost-effectiveness analysis will be performed alongside the stepped wedge trial. The Health care Institute of the Netherlands (ZIN) 2016 guideline for economic evaluations forms the basis of the analysis [19]. Healthcare consumption from inclusion to final follow-up of the patient is measured. This is in line with the measurement pathway of the clinical study. Healthcare consumption is multiplied by unit costs associated with healthcare consumption. Also, productivity-related costs seem to play an important role. Therefore, the societal perspective is the base case. A healthcare perspective is used as the scenario. These will be measured using a selection of questions of the medical consumption questionnaire (iMCQ) and the productivity costs questionnaire (iCPQ). These questions will be asked after 1 and 6 weeks, 6 months, and 1 year. The costs and for example months not working will be compared for the two different condition groups.Acceptability of the study protocol. Measuring the actual time of plaster cast treatment and number of patients who followed the protocol. If not following the protocol (condition A or B), reason for violation of the protocol. The answers to these questions will be gathered at the end of the study by provided information from the hospitals and questions asked to the participating physicians. All patients who gave informed consent will be checked if they follow the correct protocol. If they did not follow the protocol, information will be gathered why the protocol was not followed. Additionally, questions will be asked to the participating centers (local head of research). The questions asked are about feedback to the study, if they will implement the interventional treatment, why they will or will not implement the treatment, what changes to the treatment they would make, etc. The number of protocol violations and comments will be compared for both groups.

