## Discussion

This publication presents an implementation study with the use of a randomized multicenter stepped wedge design for the use of 1 week of plaster cast immobilization after non-reduced DRF. This study will be used to implement 1 week of plaster cast immobilization in several hospitals. In addition, this study tries to answer the question whether 1 week of plaster cast gives lower PRWE scores, better patient satisfaction, earlier return to work, and lower costs and if it will have the same complication rate.

A limitation of this study is the variability in clinical judgment when to reduce a DRF and thereby the chance of bias due to the surgeon’s decision who expects a high chance of secondary displacement. However, the variability in deciding when to reduce a DRF is part of common daily practice. A second limitation may be the choice for a stepped wedge design instead of a randomized controlled trial. During the feasibility study, we encountered a lot of problems with patient cross-over, difficulty performing the study for the hospitals and a large number of patients who did not want to participate in the study. By using a stepped wedge design, we think the problems with the treatment protocol will be less variable. In addition, the greater variability in deciding when to reduce a DRF leads to the exclusion criteria which will be used in general practice. Therefore, this study will give an answer which can be directly translated into daily practice.

The strengths of this study are the pragmatic nature of this study, the fact that it is an implementation study (using the Dutch guideline) in combination with a comparative study, and the use of a cost-effectiveness analysis. The pragmatic nature of this study, using a stepped wedge design, leads to a very clear protocol to use for every hospital. A clear and easy protocol is necessary as this study is an implementation study. In addition, with this study design, we can include 440 patients in 1-year time. A cost-effectiveness analysis will be performed which will give extra evidence for the effectiveness of 1-week plaster cast immobilization. Other strengths of the study are the validated primary outcome measure (PRWE) and taking into account psychological views of post-traumatic pain using the PCS-4.

As this is an implementation study, we hope the results of this study will be used for the implementation of 1-week plaster cast immobilization for non-reduced DRF nationally.

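### Complication rate is given two incompatible analyses, and the one suited to a yes/no outcome ignores cluster and calendar period

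*Protocol article*

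**What the plan says.** All the relevant rules are in one paragraph of the protocol article's Statistical analysis section.

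- One regression is named: "A multivariate linear regression mixed model will be used to analyze the data from the different randomization groups". It is meant to account for clustering within patients, hospitals and time.
- The next sentence says the intervention effect will be analysed "on the PROs, return to activity, pain scores, and complication rate". No other regression is named.
- Two sentences later: "The difference in complication rate will be determined using either a Fisher exact or a chi-square test". The choice between the two tests depends on the size of the results.
- The paragraph does not say which complication analysis carries the conclusion.

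Elsewhere, the Hypotheses section states that complications will not differ between the conditions, and the Discussion lists among the trial's questions "earlier return to work, and lower costs and if it will have the same complication rate".

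For return to activity, the Measurements section says of the productivity questionnaire: "These questions will be asked after 1 and 6 weeks, 6 months, and 1 year". For missing data in patients who completed the study, the plan is to use what is available and otherwise that "the missing data will be imputed with replacement values using multiple imputation analysis". Nothing is said about a patient who has not returned by the end of follow-up.

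**The concern.** Complications are scored as present or absent. A linear mixed model assumes roughly normal residuals with constant variance. With uncommon events neither assumption is reasonable, and fitted risks can fall below zero. Fisher exact and chi-square tests do suit a binary outcome, but they pool all usual-care patients against all intervention patients as if they were independent and recruited together. In a stepped wedge they are neither: patients are nested in clusters, and condition is tied to calendar time by design.

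At stake is the safety side of the trial's message, that shortening immobilisation leaves complications unchanged. The two methods can give different answers, and the plan does not say which will be reported. If the simple test is used, a drift in complications over the recruitment year could appear as an effect of the intervention or could hide one.

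**Working it through.** **Inputs.** Table 1 has 10 clusters and 12 periods of 4 weeks. Cluster i is in usual care (A) in periods 1 to i, in transition in period i+1, and in the intervention (B) in periods i+2 to 12. The expected intake is equal across cells: four patients per cell in the Design section, three in the Power analysis.

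**Check against the plan's totals.** A cells: 1+2+…+10 = 55. B cells: 10+9+…+1 = 55. Together 110 cells. 110 × 3 = 330 and 110 × 4 = 440, both as stated in the Power analysis, so the layout is read correctly.

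**Mean recruitment period.**

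- A: the period numbers in cluster i sum to i(i+1)/2. Over the clusters: 1+3+6+10+15+21+28+36+45+55 = 220. Mean = 220/55 = 4.0.
- B: cluster i has 11−i cells with mean period (i+14)/2. Over the clusters: 75+72+68+63+57+50+42+33+23+12 = 495. Mean = 495/55 = 9.0.
- Gap: 9.0 − 4.0 = 5 periods = 20 weeks.

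**Overlap.** T1 and T2 hold only A cells (10+9 = 19 of 55). T11 and T12 hold only B cells (9+10 = 19 of 55). So 19/55 = 35% of the cells in each condition have no contemporaneous comparator.

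**Consequence for an unadjusted test.** Suppose the intervention has no effect and the complication risk in period t is a + d·t. With equal cells, the expected crude difference B − A is d × (9.0 − 4.0) = 5d. Any linear drift per period is thus multiplied by five and attributed to the intervention. The documents give no value for d, so this shows the mechanism and does not estimate its size. Trial status expects recruitment to run for a year from September, so on average A patients would enter roughly in early winter and B patients roughly in spring. A seasonal pattern would act in the same way.

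**The two stated methods side by side.**

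| | Suits yes/no outcome | Cluster | Period |
|---|---|---|---|
| Linear mixed model | no | yes | meant to be covered |
| Fisher or chi-square | yes | no | no |

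Neither row meets all three needs.

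**Return to activity.** No arithmetic is possible from the documents. The Measurements section says that time off work, in months, will be compared between the conditions, and the list of other study parameters includes how long a patient could not work or manage the household. Durations are therefore collected. What is missing is how a duration still running at 12 months, or cut short by loss to follow-up, enters a linear model. The Power analysis allows for 30% loss.

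**The case against.** The strongest reply on complications is that the sentence listing the outcomes does not itself name the model, while a later sentence is devoted to complication rate. On that reading the specific sentence governs and there is no conflict. This is a fair reading, but it leaves the unclustered, unadjusted test as the only effect analysis for a stated hypothesis, which is the worse of the two faults. On the other reading, two methods compete. A correction is needed either way.

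It can also be said that a journal article leaves model detail to an analysis plan. That excuses omissions, but here named methods are assigned to a named outcome.

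A third reply is that a logistic mixed model with a separate term for each of 12 periods may be unstable if complications are few. The Background reports no secondary displacement among the 40 patients of the feasibility study. This stands, and the fix has to allow for it.

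A reader might go further on return to activity and infer that it is known only as returned or not at each questionnaire, that patients not yet returned have no usable value, and that the estimate would be wrong by some number of weeks. The documents do not support this. Durations are collected, and a patient followed to one year without returning still has a duration of at least 12 months. Nowhere does the plan say that such patients are dropped or that questionnaire dates are taken as exact return times. Any figure for the distortion would rest on assumed return times and an assumed coding rule.

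**Conclusion.** The point holds for complications. The paragraph offers a linear model unsuited to a binary outcome and a simple test that disregards cluster and period. The imbalance in calendar time follows exactly from Table 1: mean period 4.0 against 9.0, or 20 weeks, given equal recruitment per cell. How large a bias results depends on a time or season trend in complications that the documents do not give; with no trend, the bias from ignoring period would be nil.

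For return to activity only a minor point remains: a linear model is stated with no rule for patients not returned by 12 months or lost earlier. Calling the outcome unusable, or putting a number on the error, goes beyond the text.

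These are secondary analyses. The sample size rests on the PRWE at 6 weeks and is unaffected.

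**What to change.** In the Statistical analysis section:

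1. Name one effect analysis for complications: a logistic mixed model with a random effect for the randomised cluster (the ten clusters, since some combine hospitals) and adjustment for period. State in advance that a penalised fit or a coarser period term will be used if events are few.
2. Keep the Fisher exact or chi-square result as descriptive only, and take complication rate out of the list under the linear model.
3. In the same edit, reconcile the sentence that assigns a t-test to VAS, PCS-4 and satisfaction. Pain scores also appear in the list under the mixed model, and a t-test ignores cluster and period in the same way.
4. For return to activity, define the collected duration as the variable and analyse it with a clustered, period-adjusted method that treats patients not returned by 12 months, or lost earlier, as censored.

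The cost is wording only: recruitment had not started according to Trial status, and neither data collection nor sample size changes. The price is an odds ratio for complications with wider intervals than the crude comparison, and possible instability if events are sparse.

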### Design

The present study is a multicenter randomized stepped wedge trial. Patients with a DRF treated non-operatively and without performance of a closed reduction will be included in the study.

This stepped wedge trial will include 10 clusters, expecting to include 4 patients per cluster per time period of 4 weeks (Table 1). Every cluster will be randomized to a step: the moment when a cluster will start with the study. A transition period of one time period of 4 weeks is added between conditions A and B. This transition period is meant for explaining the treatment and to give instructions to the hospitals and caregivers to re-organize the treatment protocols.

**Table 1 Tab1:** Design Cast OFF-2, stepped wedge design

Cluster	T1	T2	T3	T4	T5	T6	T7	T8	T9	T10	T11	T12
1	A		B	B	B	B	B	B	B	B	B	B
2	A	A		B	B	B	B	B	B	B	B	B
3	A	A	A		B	B	B	B	B	B	B	B
4	A	A	A	A		B	B	B	B	B	B	B
5	A	A	A	A	A		B	B	B	B	B	B
6	A	A	A	A	A	A		B	B	B	B	B
7	A	A	A	A	A	A	A		B	B	B	B
8	A	A	A	A	A	A	A	A		B	B	B
9	A	A	A	A	A	A	A	A	A		B	B
10	A	A	A	A	A	A	A	A	A	A		B

*A*, usual care, 4–5 weeks of plaster cast treatment; *B*, 1 week of plaster cast treatment

An inclusion of 4 patients per cluster per month is expected. Before starting this study, every hospital needs to indicate the number of patients seen per month with a DRF who are treated non-operatively. Hospitals of which the expected number of patients will be less than 4 patients per month will be combined to one cluster. By adapting the study protocol based on the expected available patients, we expect that all clusters will reach sufficient inclusions.

Randomization will be performed to determine when a cluster will start with the study. The study period for every included patient will be 1 year. Follow-up of the included participants is the same for both groups: conditions A and B.

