### Investigational treatment

All clusters will start simultaneous with their usual treatment: condition A. After 1 week of plaster cast, patients will be seen at the outpatient clinic, a physical examination will be performed, and a prolonged plaster cast will be provided (another 2–4 weeks).

During the second follow-up visit at the outpatient clinic, the plaster cast will be removed, the duration of immobilization with the plaster cast will be registered, a physical examination will be performed, and extra questions on function and pain will be asked. After removal of the plaster cast, information is given about the importance of using their arm and performing the exercises of the home exercise program.

When the cluster/hospital is randomized to switch treatment, all patients will be treated following condition B. Patients in condition B will have an immobilization period of 1 week. Patients will get a splint or cast at the emergency department. After 1 week, an appointment is scheduled at the outpatient clinic. Instead of a plaster cast change, the splint or cast will be removed and physical examination will be performed. After the removal of the plaster cast, information is given about the importance of using their arm and doing the exercises of the home exercise program. Four to 5 weeks post-injury, patients will have a second follow-up appointment at the outpatient clinic where a physical examination will be performed and additional questions on function and pain will be asked. When patients did not give informed consent for use of their medical files and filling in questionnaires, they will still be treated by the protocol the hospital is using at that moment. That can be condition A or B.

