### Power analysis

We used the stepped wedge sample size tool in STATA.

A sample size of 330 patients was calculated with a power of 0.85, alfa of 0.05, and *ICC* of 0.01. We designed the stepped wedge for ten clusters with three patients per cluster per time period (Table 1). We used results from our pilot study for the reference values. The Patient-Rated Wrist Evaluation (PRWE) scores after 6 weeks were used as this will be one of our most important outcomes and have a validated clinical difference score. We used a PRWE score of 35 for the control group and 25 for the intervention group. A difference of around 10 points is needed to reach a relevant clinical difference [18]. In order to account for a 30% loss to follow-up, we aim for a sample size of 440 patients, i.e., four patients per cluster per time.

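### Calendar period is not stated as a fixed effect, so a calendar trend in this one-way stepped wedge would be partly credited to 1-week casting

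*Protocol article*

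**What the plan says.** **Design.** The Design section states "Every cluster will be randomized to a step: the moment when a cluster will start with the study" and "This stepped wedge trial will include 10 clusters, expecting to include 4 patients per cluster per time period of 4 weeks". Investigational treatment adds "All clusters will start simultaneous with their usual treatment: condition A". Each cluster later switches to B and never returns. Between the two, "A transition period of one time period of 4 weeks is added between conditions A and B", shown as a blank cell per cluster in Table 1.

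**Analysis.** The Statistical analysis section plans a linear mixed model "to account for clustering of repeated measurements within patients and within hospitals and time". On covariates it says "We will adjust for confounding factors such as age, gender, and clinical parameters". The model is meant for the patient-reported outcomes, return to activity, pain scores and complication rate. The same paragraph then assigns simple two-group tests. Complications get a Fisher exact or chi-square test. For three scores, "The difference in PCS-4 score, VAS score, and patient satisfaction will be determined using a" t-test. The document nowhere states a fixed effect for calendar period or step.

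**Power.** The Power analysis section says "A sample size of 330 patients was calculated with a power of 0.85, alfa of 0.05", with ICC 0.01, ten clusters, three patients per cluster-period and PRWE at 6 weeks of 35 against 25. No SD is given.

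**The concern.** Randomising the switch date does not balance A and B over calendar time. A is early and B is late in every cluster. The comparison is protected only if it is made within calendar periods, and that requires a period effect in the model.

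The wording on time can be taken in several ways, and the most literal ones do not give this protection:

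- **Follow-up visit.** This describes time since injury and leaves calendar trend untouched.
- **Random period effect.** The period estimates are shrunk towards zero, so only part of a trend is removed.
- **Hospital-by-period clustering.** This widens the error structure but leaves the shared trend in the treatment contrast.

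Season, learning in the plaster rooms or a drift in who is enrolled could each move PRWE over the recruitment year. Part of that movement would then be reported as an effect of cast duration. A trend in the other direction could hide a real effect. PRWE is a secondary outcome in the Methods, but it drives the sample size and the Discussion calls it the primary outcome measure.

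**Working it through.** **Inputs from the protocol.** Table 1 layout; 3 patients per cluster-period; ICC 0.01; difference 10; alpha 0.05 (two-sided assumed); power 0.85.

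**Assumptions.** SD 20 (range 15 to 25), and a linear PRWE trend of 0, 2, 3, 5 or 10 points from T1 to T12.

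**1. Count.** Each cluster has 12 - 1 = 11 data periods. So 10 x 11 x 3 = 330 patients, and 10 x 11 x 4 = 440. Both match the protocol.

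**2. Separation in time.** Cluster i has A in periods 1 to i, giving 55 A cells with mean period 220/55 = 4.0. By symmetry the 55 B cells have mean 13 - 4.0 = 9.0. The gap is 5 periods, or 5/11 = 45% of a T1-T12 trend in a raw comparison.

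**3. Reproducing the power.** Generalised least squares on the 110 cells, with a random cluster intercept:

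- Cluster variance is 0.01 x 20² = 4; cell error variance is 0.99 x 20²/3 = 132.
- With fixed periods the SE is 3.34. Power is Φ(10/3.34 - 1.96) = 0.85, as stated.
- Without period terms the SE is 2.27 and power is 0.993; 85% power would then correspond to SD 29.4.

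The match at SD 20 is conditional. That SD was found by solving the power statement with fixed periods.

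**4. False-positive rate with no treatment effect.** With no period term, the GLS estimate takes up about 48% of the trend. With bias b and standard error s, the rate is Φ(-1.96 + b/s) + Φ(-1.96 - b/s). For 5 points, b = 0.48 x 5 = 2.4 and b/s = 2.4/2.27 = 1.06, which gives 18%.

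The random-period and fixed-period columns come from 10,000 simulated trials per setting. For the random-period model the period variance was estimated by REML and the other variances were set at their true values.

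| Assumed trend, T1-T12 | No period term: bias, rate | Random period: bias, rate | Fixed period: rate |
|---|---|---|---|
| 0 | 0, 5% | 0, 4% | 5% |
| 2 points | 1.0, 7% | 0.9, 6% | 5% |
| 3 points | 1.4, 10% | 1.3, 8% | 5% |
| 5 points | 2.4, 18% | 2.1, 15% | 5% |
| 10 points | 4.8, 56% | 4.0, 41% | 5% |

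A small additional simulation with a hospital-by-period random effect left the bias almost unchanged from the model with no period term.

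**5. Sensitivity, 5-point trend.** From SD 25 to SD 15 the rate runs from 14% to 29% with no period term and from 11% to 24% with random period. At SD 20 and ICC 0.05 it is about 20% and 17%.

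**6. Plain t-test.** With 165 per condition, s = 20 x √(2/165) = 2.20. A 5-point trend (0.25 SD) gives b = 5 x 5/11 = 2.27 and a rate of 18%. A 10-point trend (0.5 SD) gives 54%. Clustering is ignored here. In SD units the result carries over to PCS-4, VAS and satisfaction.

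**The case against.** **The wording is ambiguous.** Time is named in the model sentence, and the clause can be read as accounting for clustering and, separately, for time. If a fixed period effect was meant, the problem in the mixed model disappears. Coding a term as fixed or random is also something a condensed article may leave to the analysis plan. This stands as far as intent goes: a reader might infer that the plan decides against period adjustment, and the text does not show that. It does not dispose of the point, because the article fixes a role for time that its literal readings leave inadequate. The t-tests and the Fisher or chi-square test are also stated outright, and they cannot carry a period term.

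**The covariate list is open.** The words introducing it make age, gender and clinical parameters examples. The article therefore names only patient factors; it does not restrict adjustment to them. Those covariates would also absorb part of any change in case mix.

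**The sample size may have assumed period effects.** The stated power fits a round SD of 20 only with fixed periods. This favours terse wording over a planned analysis without them. It is suggestive only, since the SD is not stated.

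**The inflation is conditional.** With no trend the rate is 5%, and at 2-3 points the excess is modest. A 5-point trend is half the design difference, moving in one direction for a year. Only linear trends were examined, and the documents give no evidence of any. This stands in full.

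**Conclusion.** The point holds as a conditional one. The design ties treatment to calendar time, and the article does not state the term that separates the two. At SD 20, ICC 0.01 and 330 patients, the false-positive rate for PRWE is about 6-10% for a trend of 2-3 points, 15-18% for 5 points and 41-56% for 10 points. The lower end is for a random period term and the upper end for none.

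Two stronger readings are not supported. A reader might infer that the error rate is well above 5% whatever happens; that applies only from a trend of about 5 points upward, and trend size is an assumption throughout. A reader might also infer that adding period effects costs no power; the agreement with 0.85 is built in by the way SD 20 was obtained.

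Confidence is medium, because one sentence on intent could settle the mixed-model part. The part on the simple tests does not depend on that reading.

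**What to change.** State that calendar period (T1-T12, one 4-week block each) enters every mixed model for patient-reported outcomes as a fixed categorical effect, separate from follow-up visit, with random effects for cluster (the randomised unit) and patient. Replace the t-tests for PCS-4, VAS and satisfaction, and the Fisher or chi-square test for complications, by models with the same period and cluster terms. This would also leave pain scores and complications with one method each; at present they fall under both the mixed model and a simple test.

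The change to the text is a few sentences. The statistical cost is precision: relative to no period terms the SE rises by 3.34/2.27 - 1 = 47%. With fixed periods and 330 analysed patients, power for 10 points depends on the SD:

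| SD | Power, fixed periods |
|---|---|
| 15 | 0.98 |
| 20 | 0.85 |
| 25 | 0.67 |
| 29.4 | 0.53 |

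The last row applies if the sample size was in fact calculated without period terms. The SD used should therefore be stated alongside the power, together with whether the calculation included period effects.
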